## Abstract

**Background:**

Individuals with cerebral palsy (CP) have problems in everyday tasks such as walking and climbing stairs due to a combination of neuromuscular impairments such as spasticity, muscle weakness, reduced joint flexibility and poor coordination. Development of evidence-based interventions are in pivotal role in the development of better targeted rehabilitation of CP, and thus in maintaining their motor function and wellbeing. Our aim is to investigate the efficacy of an individually tailored, multifaceted exercise intervention (EXECP) in children and young adults with CP. EXECP is composed of strength, flexibility and gait training. Furthermore, this study aims to verify the short-term retention of the adaptations three months after the end of the EXECP intervention.

**Methods:**

Twenty-four children and young adults with spastic CP will be recruited to participate in a 9-month research project with a 3-month training intervention, consisting of two to three 90-min sessions per week. In each session, strength training for the lower limbs and trunk muscles, flexibility training for the lower limbs and inclined treadmill gait training will be performed. We will evaluate muscle strength, joint flexibility, neuromuscular and cardiometabolic parameters. A nonconcurrent multiple baseline design with two pre-tests and two post-tests all interspaced by three months is used. In addition to the CP participants, 24 typically developing age and sex-matched participants will perform the two pre-tests (i.e. no intervention) to provide normative data.

**Discussion:**

This study has a comprehensive approach examining longitudinal effects of wide variety of variables ranging from physical activity and gross motor function to sensorimotor functions of the brain and neuromuscular and cardiometabolic parameters, providing novel information about the adaptation mechanisms in cerebral palsy. To the best of our knowledge, this is the first intervention study providing supervised combined strength, flexibility and gait training for young individuals with CP.

**Trial registration number:**

ISRCTN69044459, prospectively registered (21/04/2017).

## Background

### Cerebral palsy

Cerebral palsy (CP) describes a group of permanent disorders of the development of movement and posture, that are attributed to nonprogressive disturbances that occurred in the developing fetal or infant brain [1]. The spastic-type CP accounts for approximately 80% of all CP cases [2–4] and is characterized by hyper-resistance [5] which has three components: stretch hyperreflexia (i.e. velocity dependent involuntary activation), involuntary background activation and altered muscle-tendon mechanical properties. Muscle-tendon unit mechanical alterations [6–8] can cause severe reduction in joint range of motion (i.e. contractures) and lead to bone deformation [9–11]. The development of contractures does not seem to be caused solely by hyperreflexia [12, 13]; rather muscle inactivity and impaired muscle growth seems to be important factors [14, 15]. Furthermore, another debilitating symptom in CP is a decreased muscle strength [6, 16–18] that severely hinders the ability to perform tasks such as walking and climbing stairs [19–21]. These secondary clinical symptoms induce lower physical activity (PA) levels in people with CP [22, 23] and lead to higher levels of body adiposity and other cardiometabolic risk factors [16, 24, 25]. Therefore, although the initial brain lesion is nonprogressive in CP, secondary symptoms such as reduced muscle strength and joint range of motion (ROM) typically further deteriorate with time, increasing sedentarism and creating a cycle of inactivity and loss of function [26, 27]. Thus, well targeted therapeutic interventions to reduce these secondary problems and maintain motor function are in pivotal role to enable independent mobility in individuals with CP and thus support their lifelong health and wellbeing.

### Strength training for CP

Cross-sectional studies demonstrated that muscle strength had a high shared variance with gait and motor function in CP (r^2^ = 50–60% [28, 29];). Furthermore, the effectiveness of strength training complying with known training guidelines [25, 30, 31] to increase muscle strength in individuals with CP has been well demonstrated [32–40]. Nevertheless, these interventions have reported no changes [33, 35–38] or improvement in motor function [32, 34, 35]. This controversy seems to arise from two main reasons. Firstly, functional tasks involve a complex interaction between muscle strength, joint flexibility (i.e. maximum joint ROM) and motor coordination. Secondly, the neural and morphological adaptations are highly specific to the strength training methods [35, 41], which varied in these studies. A final remark is that every day functional tasks involve activation of several muscle groups spanning across joints. Thus, an adequate intervention should train all relevant muscles with naturalistic patterns of neural activation.

A major yet unproven concern is that strength training could increase hyper-resistance and thus would be an unadvisable intervention [42]. Only few strength training studies have measured components of hyper-resistance longitudinally and reported no changes after the intervention [33, 34, 37, 38]. Furthermore, the term “spasticity” is often used under varied definitions and assessment methods [43]. For example, the modified Ashworth Scale [44] utilized in two of these studies [33, 34] is a subjective assessment of resistance to passive movement [45]. Scholtes et al. [37, 38] evaluated hyperreflexia by assessing the presence of a catch (i.e. sudden increase in muscle tone) in response to a single fast (< 1 s) passive stretch, being also a subjective measure of the velocity-dependent resistance to passive movement. Both measurements fail to differentiate between the different components of hyper-resistance. Therefore, although it is generally accepted that strength training does not increase “spasticity” [46], no longitudinal study has reported an objective, valid and reliable measurement of hyper-resistance.

### Flexibility training for CP

Stretching is often utilized to prevent or treat loss of joint flexibility, however a recent systematic review pooling different stretch modalities (e.g. splint, serial casting, manual therapy) for different patient groups (e.g. CP, stroke, spinal cord injury) reported high-quality evidence that it does not have clinically relevant effects [47]. Passive stretching has the advantage of not restricting joint movement for a prolonged time as opposed to serial casting or splints, however, its effectiveness to increase joint flexibility in people with CP is unclear [48, 49]. Theis et al. [50] demonstrated that passive dorsiflexion stretching caused an acute increase in flexibility due to the elongation of both muscle and tendon. However, comprehensive longitudinal data is scarce. Theis et al. [51] showed an increase in dorsiflexion flexibility after a 6-week passive stretching intervention (4 days per week, 15 min per day). Zhao et al. [52] demonstrated that passive dorsiflexion stretching and active ankle joint movement within a 6-week intervention was able to increase fascicle length of both soleus (Sol) and medial gastrocnemius (MG). However, the study did not have a control group and the sample was composed of children, thus maturation may have been an intervening variable. The disparity between the limited scientific understanding of stretching effectiveness for CP and its widespread utilization must be addressed swiftly.

### Gait training for CP

The inability to dorsiflex the ankle joint during the stance phase (i.e. toe walking) and swing phase of gait (i.e. foot drop) are common problems in CP [53]. A recent literature review has concluded that gait training is safe, feasible and effective to improve walking ability in children and young adults with CP [54]. The incline treadmill setup seems particularly effective as it forces a greater ankle dorsiflexion in the swing phase and serves as a dynamic passive stretch for the ankle plantarflexors in the stance phase [55, 56]. Daily gait training with an inclined treadmill has been demonstrated to increase walking speed, dorsiflexion strength and active ROM, and reduce ankle stiffness in only four to six weeks [57, 58]. No changes in ankle passive flexibility were found in these studies, however the decrease in passive stiffness suggests that the muscle-tendon unit is adaptable, but further improvements in ROM may require a longer period of training. It is noteworthy that altering gait pattern and automatizing it for use in everyday over ground walking may require intense individualized feedback, so the person is aware or is at least guided towards the correct pattern (e.g. verbal feedback, biofeedback/augmented reality; [54]).

### Study purpose

The present study has three aims: 1) to investigate the effects of the EXECP intervention on the following variables: gait performance (primary outcome), physical activity level, lower limb muscle strength and joint flexibility, gross motor function, cardiometabolic risk factors, neuromuscular parameters for triceps surae muscle, cortical processing of proprioceptive stimuli evoked by passive ankle dorsiflexions, tibialis anterior (TA) cortico-muscular and intramuscular coherence; 2) to evaluate the retention of the adaptations induced by the intervention after three months; 3) to compare CP and typically developing (TD) individuals in all studied variables using group and matched (age/sex) individual data. The EXECP intervention is composed of a three-month individually tailored exercise intervention containing strength training targeting lower limb and trunk muscles, combined with stretching of diagnosed short muscles and gait training. The primary hypothesis is that the EXECP intervention will enhance gait performance by: a) increasing walking distance in the 6 min walking test; b) increasing ankle dorsiflexion during the swing and stance phase of gait; c) increasing maximal walking velocity, joint net moments and ranges of motion in the lower limb joints. The secondary hypothesis are that the EXECP intervention will: d) increase habitual PA; e) increase maximal isometric and concentric torque and rate of force development for the trained muscles; f) not affect cardiometabolic risk factors such as arterial stiffness, insulin resistance, blood lipids and body fat content; g) increase gross motor function measure (GMFM; [19]) score; h) increase lower limb joint flexibility of the trained muscle groups; i) decrease ankle plantarflexors average joint stiffness and increase joint energy (i.e. area under the torque-angle curve) during slow passive stretching; j) decrease antagonist muscle electromyography (EMG) during maximal voluntary isometric and concentric plantarflexion and dorsiflexion; k) not change spinal mechanisms related to hyperreflexia in the Sol muscle (i.e. Hoffmann-reflex (H-reflex), post-activation depression (PAD) ratio, tonic stretch reflex threshold (TSRT)); l) increase amplitude of cortical responses to proprioceptive stimulation, recorded with magnetoencephalography (MEG) in the primary somatosensory cortex; m) increase cortico-muscular coherence between cortical MEG and TA EMG signals; n) increase intramuscular coherence within TA muscle during a submaximal isometric dorsiflexion and during the swing phase of the gait cycle. No changes in any of the studied variables are expected during the 3-months control period, except if the participant is going through the growth spurt. After the 3-month maintenance period, the values of the studied variables are expected to be in between the control and post intervention values (project aim B). All study variables are hypothesized to show differences between the TD and CP groups (project aim C). It is expected that the comprehensive assessment battery of neuromuscular, brain, cardiometabolic and functional parameters will add valuable information about how people with CP adapt to exercise.

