### Statistical analyses

Mean/median values, standard deviations and 95% confidence intervals will be reported. Normality of data will be tested using the Shapiro-Wilk test. General linear mixed model analysis will be utilized to study the differences between time (2 pre-tests and 1 or 2 post-tests) in the CP group. Independent t-tests will be used to compare groups (i.e. CP vs. TD) and paired t-tests to compare the two TD testing times (pre-test 1 and 2). Pearson correlation analysis will be performed to check association between dependent variables. The interference of variables such as PA levels or maturity offset will be controlled if they have a strong linear relationship with other dependent variables. Nonparametric tests may be utilized if necessary. Significance level will be set at *P* < 0.05.

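### Hypotheses f and k predict no change, but the plan gives them only tests for a difference at P < 0.05 and no margin, so its analysis can refute them but not support them

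*Protocol article*

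**What the plan says.** Most of the lettered hypotheses under Study purpose are directional, but two predict absence of effect. Hypothesis f is that the intervention will "f) not affect cardiometabolic risk factors such as arterial stiffness, insulin resistance, blood lipids and body fat content". Hypothesis k is that it will "k) not change spinal mechanisms related to hyperreflexia in the Sol muscle", measured by the Soleus H-reflex, the post-activation depression (PAD) ratio and the tonic stretch reflex threshold (TSRT).

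Statistical analyses gives one framework for every variable. For the CP group, "General linear mixed model analysis will be utilized to study the differences between time"; t-tests serve the other comparisons, with nonparametric tests if needed. The rule is "Significance level will be set at *P* < 0.05". Means or medians, standard deviations and 95% confidence intervals will be reported.

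No smallest relevant change or margin is given for any f or k variable. The only such figure in the document, a factor of 1.08, belongs to the six-minute walking test (6MWT) and is used only under Sample size.

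The section Strength training for CP explains why k is there: "A major yet unproven concern is that strength training could increase hyper-resistance". It notes that earlier studies found no change but used subjective measures.

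**The concern.** A difference test takes no change as its null hypothesis. Rejecting the null contradicts f or k. Not rejecting it leaves open whether there was no change or whether the study was too imprecise to see one. Under such a rule, the noisier the reflex or blood measure, the safer the hypothesis.

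The stake is highest for k. The Background criticises earlier null findings on hyper-resistance for their measurement methods. This trial brings objective measures, but one more non-significant result, with no statement of how large a change it excludes, would leave the question open.

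**Working it through.** **Inputs from the protocol article.** 24 CP participants and alpha 0.05 (Sample size; Statistical analyses). Sidedness is not stated, so two-sided is assumed.

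**Assumptions.** The documents give no SD of change and no relevant change for the H-reflex, PAD ratio, TSRT or cardiometabolic variables. Effects are therefore expressed in SDs of the within-person change score, over a range. A paired t-test stands in for one pre-to-post contrast of the mixed model, with complete data.

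**The plan's own figure.** The 24 comes from the 6MWT, not from f or k. With SD of change √2 × ln 1.06 = 0.0824 and difference ln 1.08 = 0.0770, the normal formula gives 2 × (0.0824 × (1.960 + 0.842) / 0.0770)² ≈ 18 per group, or 20 with the t distribution. The plan calls its 24 an upper bound, so this gap is not shown to be an error. 24 is taken as given below.

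**Step 1: what the difference test misses.** Power is taken from the noncentral t distribution with 23 degrees of freedom and noncentrality d × √24.

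| True change (SD of change) | Power | Missed |
|---|---|---|
| 0.2 | 16% | 84% |
| 0.3 | 29% | 71% |
| 0.4 | 47% | 53% |
| 0.5 | 65% | 35% |
| 0.6 | 80% | 20% |

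**Step 2: what the planned interval excludes.** The half-width of the 95% interval is 2.069 / √24 = 0.42 SD. Even an observed change of exactly zero leaves true changes up to 0.42 SD in either direction unexcluded. Whether that is reassuring depends on a margin that the plan does not give.

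**Step 3: what an equivalence analysis could show.** The rule is two one-sided tests (TOST): the 90% interval, half-width 1.714 / √24 = 0.35 SD on average, must lie inside the margin. Power by simulation, with no true change:

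| Margin (SD of change) | Power, n = 24 |
|---|---|
| 0.3 | 2% |
| 0.4 | 22% |
| 0.5 | 54% |
| 0.6 | 77% |
| 0.65 | 85% |
| 0.8 | 97% |

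By the normal approximation, 80% power needs ((1.645 + 1.282) / margin)² people: about 35 for 0.5 SD, 96 for 0.3 SD and 215 for 0.2 SD.

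**Step 4: sensitivity to dropout.** With 20 completers (an illustrative figure), difference-test power falls to 0.397 at 0.4 SD and 0.565 at 0.5 SD. TOST power falls to 0.392 at a 0.5 SD margin and 0.653 at 0.6 SD.

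**The case against.** **Nothing in the article says that P > 0.05 will be read as proof of no change.** A reader might infer it from null hypotheses paired with a significance rule, but the document does not state it. This stands, and the point is limited to what the analysis can support.

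**95% intervals are planned.** They would show a careful reader what has not been excluded. This softens the problem. Without a margin it does not solve it, because no width or position of the interval counts for or against f or k.

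**Margins may sit in a fuller document.** A journal article condenses, and an absent margin alone would not be a finding. But this article states both the hypotheses and the testing rule, and the two do not fit together.

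**The SD figures are assumed.** This is correct. At 0.5 SD the test detects a change more often than it misses one, and whether 0.4 to 0.6 SD matters for these variables is unknown. That is itself a reason to fix a margin.

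**The control period and the 6MWT.** A reader might extend the point to the statement that "No changes in any of the studied variables are expected during the 3-months control period", or to the 6MWT. The documents do not support either extension.
- Stability in the control period is an expectation with a growth-spurt exception, not a lettered hypothesis. No analysis depends on a non-significant comparison of the two pre-tests, and the Discussion openly considers that they may differ.
- For the 6MWT the precision is ample. The 95% half-width is 2.069 × 0.0824 / √24 = 0.035, about 3.5%, against the plan's own 8%. That 8% equals 0.0770 / 0.0824 = 0.93 SD of change, where TOST power is about 99%. A 3% drift would be non-significant 61% of the time, but it lies well inside 8%, and a TOST at 8% would itself call it stable about 86% of the time.

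**Conclusion.** The point holds for hypotheses f and k only. As written, the analysis can contradict them but can never provide evidence for them, and 24 participants are too few for a non-significant result to be informative about small to moderate changes: 53% of true 0.4 SD changes and 35% of true 0.5 SD changes would be missed. These figures rest on the assumed SD units, a two-sided paired comparison and complete data.

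The primary outcome, the sample size and the directional hypotheses are not affected. Because k bears on a concern that the protocol itself raises, the change should be made, although both hypotheses are secondary.

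**What to change.** **Set margins.** Before the data are analysed, name the key variables under f and k and give each a margin based on the smallest relevant change. Measurement error alone should not set it, since a margin that widens with noise would again reward imprecision. Testing sessions also says that only some tests are repeated at familiarisation, so repeatability may not be available for every variable.

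**State the rule.** Claim no change only if the 90% interval for a named pre-to-post contrast lies inside the margin (TOST). Otherwise report the result as inconclusive, or as a change if the difference test shows one.

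**Where no margin can be justified,** reword f or k as estimation with the 95% intervals already planned, and state that non-significance is not evidence of no change.

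**For the hyper-resistance concern,** the upper confidence bound against an increase may be reported in addition. One-sided power at 24 people, with no true change, is 77% for a 0.5 SD margin and 89% for 0.6 SD. It cannot replace the two-sided assessment, because k predicts no change in either direction.

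**Cost.** A short margin table and revised wording, with no new data. Study design defers data analysis, flexibility tests apart, until collection ends, so margins for f and k can be set without knowledge of their results. The downside is that some no-effect claims will become inconclusive: TOST power is 54% at a 0.5 SD margin and 77% at 0.6 SD.

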
## Methods

### Study design

The present study utilizes a nonconcurrent multiple-baseline design [59, 60] composed of two pre-tests interspaced by three months (i.e. control period), followed by the three-month EXECP-intervention, and two post-tests performed immediately after and three months after the intervention (i.e. maintenance period; Fig. 1). The TD age and sex-matched control group will be tested in the two pre-tests without the intervention. The nonconcurrent multiple baseline design was selected over the randomized controlled trial (RCT) because the participants inside the inclusion criteria are expected to form a highly heterogeneous group regarding the studied variables (e.g. motor control, muscle strength, joint flexibility and gait mechanics), and randomly dividing the sample into two groups is not likely to result in two comparable groups. The chosen experimental design circumvents the expected high variability in the studied variables by allowing the subjects to be their own controls. Additionally, it allows performing the EXECP intervention all year-round, avoiding systematic seasonal influences to affect the study variables (e.g. vacations, seasons [61];). During the participation in the project, both groups will perform their normal activities (i.e. physiotherapy and/or sport activities), with the instruction of maintaining the number of sessions and activity type as stable as possible. Exceptionally during the intervention period, a reduction in the volume of the activities may be necessary to avoid overloading the participants. Any important deviations from the activities done during the control period will be reported. The first author will be responsible for all tests, and it is not possible to blind him to group allocation. Testing procedures were defined in detail to ensure consistency. The outcome data is quantitative and objective, with little possibility to suffer from observer bias. However, because the tester will obviously hope for better results in the Post-tests, no data analysis will be performed before the data collection is done (except for the flexibility tests). Thus, the tester will not have any knowledge of the results and will be focused on implementing the tests according to the protocol.

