### Sample size

Power calculation was performed for the project’s primary hypothesis (i.e. gait performance), specifically for the effect of the EXECP intervention on walking performance measured by the six minutes walking test (6MWT [63];). The distance covered in the 6MWT is reported to reflect functional capacity and has been recommended as a submaximal exercise test for children with CP of GMFCS I to III [64, 65]. Results from Pre-tests 1 and 2 for the first 9 participants in the project were utilized for sample size calculation utilizing an online spreadsheet (www.sportsci.org [66];). Data was log-transformed due to the inexistence of zero and negative values, yielding a typical error of 1.06, between-subject SD of 1.46 and a smallest important change of 1.08. Utilizing the pre-post parallel-groups RCT model, with a power of 0.8 and an alpha of 0.05, a sample size of 24 participants in both CP and TD group is required. No specific sample size calculation algorithm for our experimental design was found, thus the RCT calculation served as an upper bound for the sample size.

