Stretch hyperreflexia of Sol and MG will be assessed utilizing the TSRT [88, 89]. The participant will be seated with the knee joint fully extended and the ankle dynamometer previously described will induce stretches (from 20° of plantarflexion to 0°) on triceps surae at four different velocities: 50, 100, 200 and 300°/s. The stretch velocities will be delivered in a pseudo-randomized and balanced order, yielding 10 stretches in each velocity, with an interval of 2.6–2.9 s. EMG data will be used to determine the joint angle in which the stretch reflex onset occurred (i.e. dynamic stretch reflex threshold, DSRT). A regression line based on a first-order linear equation using all DSRT will be calculated on a stretch velocity-joint angle plot. From the equation, the coefficient of determination, slope and intercept with the x-axis will be attained. The TSRT is the angle at which the regression line intersects with the x-axis, larger values indicate a high level of stretch hyperreflexia. TSRT will be calculated separately for each muscle. In addition to the already established TSRT calculation, we propose using the latency of the H-reflex to take into account the time between the stretch reflex onset and the EMG burst onset. A typical H-reflex latency of 35 ms and a stretch velocity of 300°/s can cause a difference of 10.5° between the stretch reflex and EMG onset, provoking a systematic error towards higher velocities. Thus, all variables in the TSRT will be calculated with and without the latency correction, and the differences will be discussed. Participants will be instructed to relax and will be wearing noise blocking headphones. Trials with EMG exceeding 5% of the isometric plantarflexion MVC in the 500 ms preceding the stretch will be discarded. The EMG burst onset will be defined as a 3SD increase in the RMS of a 20 ms moving average for at least 20 ms compared to the pre-stretch state. Visual inspection of false positives due to small brief muscle activations will be performed and automated onset detection algorithms may also be utilized. H-reflex, PAD and TSRT will be assessed on the most affected limb of the CP group and in the same leg of the age/sex matched control.

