#### Gross motor function

Gross motor function will be assessed in the CP group using the 66-item version of the Gross Motor Function Measure (GMFM-66; [111]). GMFM-66 is a valid, reliable and responsive observational instrument, based on interval scaling to evaluate changes in gross motor function in participants with CP [19]. Dimensions D (standing) and E (walking, running and jumping) will be utilized. The test will be video recorded and scored subsequently by the same evaluator. Absolute and relative (i.e. percentage of maximum) scores for each dimension will be reported.

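### The rule of no analysis before data collection ends was not kept for the Pre-test 6MWT data, and the claim that outcomes are objective does not fit the video-scored GMFM-66

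*Protocol article*

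**What the plan says.** The Study design section of the protocol article deals with observer bias directly. On blinding it says "The first author will be responsible for all tests, and it is not possible to blind him to group allocation". It admits that this tester will want the Post-tests to come out better, and it offers two protections.

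- The nature of the outcomes: "The outcome data is quantitative and objective, with little possibility to suffer from observer bias".
- A rule on timing: "no data analysis will be performed before the data collection is done (except for the flexibility tests"). From this it concludes: "Thus, the tester will not have any knowledge of the results and will be focused on implementing the tests according to the protocol".

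Two other sections bear on these statements.

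- Sample size: "Results from Pre-tests 1 and 2 for the first 9 participants in the project were utilized for sample size calculation". The calculation was made "specifically for the effect of the EXECP intervention on walking performance measured by the six minutes walking test", and the 6MWT distance is the primary outcome.
- Gross motor function: the GMFM-66, described there as an observational instrument, is assessed in the cerebral palsy (CP) group only. Of the recording it says: "The test will be video recorded and scored subsequently by the same evaluator".

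**The concern.** In a single-group before-after comparison with an unblinded tester, the stated safeguards against observer bias carry much of the weight. One of them, the rule on analysis, conflicts with what the article reports was done with the primary outcome. The other, objectivity, is stated for the outcome data as a whole but does not describe an instrument rated by an observer.

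Hypothesis (g) in the Study purpose section predicts that the GMFM score will rise. If the person scoring a video knows that it is a Post-test video, borderline items may be scored in the expected direction. Such a shift would look the same as an intervention effect. At stake are the credibility of the GMFM result and the accuracy of the article's account of how knowledge of results was controlled.

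**Working it through.** No effect size can be calculated here, so the check sets the sections side by side.

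**1. Was 6MWT data analysed before collection ended?**

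- The Sample size section reports a typical error of 1.06 and a between-subject SD of 1.46, as factors after log transformation, from the Pre-tests of nine participants.
- A typical error is the SD of the Pre-test 1 to Pre-test 2 change on the log scale, divided by √2 and then exponentiated. It cannot be obtained without analysing the paired results.
- The section on study sample and recruitment says recruitment had run since May 2017 and was expected to end in December 2020. The calculation is reported as already done, so it preceded the end of data collection.
- The only exception named in the rule is the flexibility tests, and the 6MWT is not one of them.

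The rule as written was therefore not kept.

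**2. Does the sample size itself matter for this point?**

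The formula is n per group = 2(z₀.₉₇₅ + z₀.₈₀)² × SD² / δ², with sidedness not stated and two-sided assumed.

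- SD = √2 × ln 1.06 = 0.0824
- δ = ln 1.08 = 0.0770
- n = 2 × 7.849 × 0.00679 / 0.00592 ≈ 18, or 20 with the noncentral t

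The article states 24. With the printed inputs moved to the unfavourable end of their rounding (1.0649 and 1.075), the same formula gives 24. The stated figure is thus compatible with unrounded inputs and is not disputed. The point here needs only the fact that the data were analysed.

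**3. What could that analysis reveal?**

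It used Pre-tests 1 and 2 only, which are the two ends of the control period. It could show variability and any control-period change. It could not show a Post-test value or an intervention effect.

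**4. Does the rule on timing protect the GMFM?**

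- Delaying analysis does not conceal whether a video comes from a Pre-test or a Post-test.
- The double baseline does not cancel scoring that depends on occasion, because both baselines can be recognised as baselines if labels are visible.
- The TD group is tested only at the two Pre-tests and has no GMFM, so it cannot reveal a shift in Post-test scoring.
- The Gross motor function section is silent on masking to occasion.

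**5. How many videos are involved?**

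The GMFM is not listed in any testing session, including the reduced Post-test 2. If it were recorded at all four test points in 24 participants, there would be 24 × 4 = 96 videos; at three points, 24 × 3 = 72. Both counts are assumptions.

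**6. Does the same apply to the EMG onsets?**

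Only weakly. The Neural parameters section says "Visual inspection of false positives due to small brief muscle activations will be performed". That check supplements a numeric rule: a 3 SD rise in a 20 ms moving RMS lasting at least 20 ms. Trials with pre-stretch activity above 5% of the plantarflexion MVC are discarded.

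**The case against.** The best reply is that the rule exists to stop hopes about Post-tests from being fed by results, and a variance estimate from Pre-tests leaves that purpose largely intact. This stands. A reader might infer that the tester saw early evidence of benefit. The article does not support that: no Post-test data were used, and it does not say who did the calculation.

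The second reply is that this is a condensed article and that masking of video scoring may be set out in the full protocol. This also stands, in that masking is unstated rather than denied. It would be wrong to say that the plan scores GMFM unmasked, that the evaluator is the tester, or that scoring is done as data arrive. Later scoring combined with the rule on timing is compatible with scoring at the end. What remains is that the article takes up observer bias and rests its case on a general claim of objectivity that does not fit this instrument.

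A reader might also extend the point to the EMG and magnetoencephalography (MEG) outcomes. For EMG, the numeric onset rule leaves limited discretion. For MEG, visual inspection marks bad channels and noisy periods before software-based cleaning, and nothing in the article shows how that would favour improvement. The MEG point is not made here.

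Detailed test procedures and a single evaluator do limit discretion, but they do not replace masking.

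**Conclusion.** The point holds in a limited form. The Study design and Sample size sections contradict each other on whether data other than flexibility were analysed before collection ended, and they must be reconciled. The practical consequence is small, because only Pre-test data were involved.

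The general claim of objectivity is too broad for the GMFM-66. Its scoring is not protected by deferring analysis and has no comparator. The size of any bias on hypothesis (g) cannot be computed from the article. This conclusion assumes that no masking is specified elsewhere; if it is, only the wording needs correcting. Nothing here bears on the 6MWT distance as an endpoint or shows the sample size to be wrong. It is a correction of the text together with a cheap improvement.

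**What to change.** 1. In Study design, add the Pre-test 6MWT analysis of the first nine participants as a second exception to the rule. State who ran it and whether the tester saw the results.
2. Limit the statement on objectivity to measures read from instruments, and name the GMFM-66 as observer-rated.
3. In Gross motor function, state that the same evaluator scores all videos after the last visit, in random order across participants and occasions, with date and occasion labels removed.
4. Optionally, use coded file names for the visual check of EMG onsets. This is secondary, because a numeric rule already applies.

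The cost is relabelling and shuffling recordings that will exist anyway, and GMFM scores become available only at the end. No extra visits, participants or evaluators are needed.
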